### Effect evaluation

#### Primary outcome

The primary outcome stress will be measured by the stress subscale of the Depression, Anxiety and Stress Scale (DASS-21) at employee level [25]. The stress subscale consists of seven questions with a score range of 0–21. These questions relate to the experience of symptoms in the past week. The stress subscale measures the level of arousal. Examples of questions are “I found that I was very irritable”, “I found myself getting impatient when I was delayed in any way (e.g. lifts, traffic lights, being kept waiting)”, and “I found it difficult to relax”. The answering categories were “Did not apply to me at all”, “Applied to me to some degree, or some of the time”, “Applied to me to a considerable degree, or a good part of time”, and “Applied to me very much, or most of the time”. The internal consistency of the scale was good (Cronbach’s α 0.85). Construct validity and criterion validity of the DASS-21 have been measured before, and the criterion validity was good [25].

#### Secondary outcomes

##### Work-related psychosocial risk factors

Psychological job demands, supervisor support, co-worker support, and decision authority will be measured at employee level using four subscales from the validated Dutch version of the Job Content Questionnaire [26]. This questionnaire measures the physical and psychological characteristics of an imbalance between job demands and resources within an organization. The questions contain a four-point scale containing the options “Totally disagree”, “Disagree”, “Agree”, and “Totally agree”. The range is 5–20 for psychological job demands (five items), 4–16 for supervisor support and co-worker support (both 4 items), and 3–12 for decision authority (three questions).

##### Psychosocial Safety Climate

The Psychosocial Safety Climate (PSC) is measured at employee level, using the Dutch translation of the PSC-12, a 12-item questionnaire that includes four topics: 1) management support for employees’ psychological health, 2) management health and safety priorities, 3) organizational interest for employee participation in health and safety issues, and 4) communication of the organization to the employees about psychological health issues [27]. The questions are answered on a 5-point Likert scale that ranges from 1 (“Strongly disagree”) to 5 (“Strongly agree”). The scale score of the PSC-12 is the sum of all 12 questions ranging from 12 to 60. The PSC-12 will be adapted for this study to represent the organizational structure of the organization under study more accurately (e.g. we will change ‘supervisor’ to ‘team coach’, since this is the term used in the organization involved).

##### Sickness absenteeism and presenteeism

Sickness absenteeism (i.e., sick leave) and presenteeism will be measured at an employee level using the questionnaire on healthcare consumption and productivity loss in patients with a psychiatric disorder (TiC-P) [28]. Sickness absenteeism will be measured with one question: “Were you off work at any time in the past 4 weeks?” (“No”/“Yes, I missed … days of work” Presenteeism, will be measured using the question: “Was your job performance adversely affected by health problems during the past 4 weeks?” (“No”/“Yes, on how many days during the past four weeks did you perform paid work although you were bothered by health problems? …….. days”. If the answer is ‘yes’, the following two questions will be asked: 1) “Please rate how well you performed on the days you went to work even though you were bothered by health problems” This will be measured on a 10-point Likert Scale with 1 for “Much worse” to 10 for “performed as usual.” 2) “If you had to catch up on work you were not able to do due to health problems during the last 4 weeks, how many extra hours would you have to work?”

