### Effect and process evaluation of Stress Prevention@Work

#### Study design and measurements

The effectiveness of SP@W will be evaluated in a cluster controlled trial. The study population consists of employees of a Dutch healthcare organization. This organization has more than 4000 employees throughout the Netherlands, who are organized in self-directing teams. The organization facilitates care in nursing homes (including geriatric rehabilitation care), residential care homes, and home-based care. SP@W will be implemented in intervention teams during the first six months of the trial period. After the final follow-up measurement (12 months after baseline), SP@W will also be offered to the control teams. Digital questionnaires will be sent to employees from both the intervention and control teams at baseline and after six and 12 months to measure the short- and long-term effectiveness of SP@W. To maximize the response rate, two reminders will be sent to the employees for each questionnaire. The questionnaires will be in Dutch. The SP@W implementation process will be assessed by performing a process evaluation. The study procedures and design have been approved by the Medical Ethics Committee of the VU University Medical Center, Amsterdam, The Netherlands (2015.480).

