### Impact of the results

A combination of several implementation strategies into one integral stress prevention strategy is important to overcome barriers at multiple levels within organizations. SP@W may lead to a reduction of stress and sick leave and an increase in productivity, which is beneficial for employees as well as for the organization.

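### As printed, the only sick-leave item does not ask about sickness, so holiday or other leave can enter the outcome; the Dutch wording needs checking

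*Protocol article*

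**What the plan says.** Under Sickness absenteeism and presenteeism, the protocol article lists the outcome among the secondary outcomes and equates it with sick leave: "Sickness absenteeism (i.e., sick leave) and presenteeism will be measured at an employee level". The instrument is the TiC-P. The section is explicit that nothing else supports the measure: "Sickness absenteeism will be measured with one question". That question is printed as "Were you off work at any time in the past 4 weeks", with a plain no or the reply "Yes, I missed … days of work".

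The presenteeism question follows directly: "Was your job performance adversely affected by health problems during the past 4 weeks". Its day count and its two follow-up questions again refer to health problems.

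Study design and measurements adds that questionnaires go out digitally at baseline, six and 12 months, and that "The questionnaires will be in Dutch". The printed English is therefore not the text respondents read.

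**The concern.** The outcome is named for sick leave, but the printed item asks about absence of any kind. A respondent who takes it literally after a holiday or a period of other leave would answer yes and enter days. Those days would be stored in the same field as sick days, with nothing to tell them apart. An analysis plan written later could not repair this, because the reason for absence is never collected.

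Sick leave matters to the trial's case. The Background uses it to show the burden of work-related stress, and Impact of the results names it among the hoped-for benefits: "SP@W may lead to a reduction of stress and sick leave and an increase in productivity". A measure that mixes in other absence would make a real effect on sick leave harder to see. If leave happened to fall unevenly between arms within the four-week window, it could also show a difference that has nothing to do with sickness.

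**Working it through.** **The plan's own figures.** The article gives no absence rate, leave rate or variance for this outcome, so there is no stated figure to reproduce. Its only computed figure is the sample size for the DASS-21 stress subscale. With a difference of 1.5, an SD of 3.81, two-sided alpha of 0.05 and power of 0.80, n per group = 2 × (1.96 + 0.842)² × 3.81² / 1.5² ≈ 101.3, so 102, against the stated 104. Also, 208 / 0.75 = 277.3, so 278, as stated. Both are in order, and neither depends on the absence item.

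**Wording side by side (as printed).**

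| Item | Restricted to health? | Reason recorded? |
|---|---|---|
| Absenteeism: question | No | No |
| Absenteeism: days-missed answer | No | No |
| Presenteeism: question and day count | Yes | Not needed |
| Presenteeism: both follow-up questions | Yes | Not needed |

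Only the absenteeism item lacks the restriction, and it is the only item for its outcome.

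**Effect on the analysis.** Let s be mean sick days per four weeks and l mean other-leave days that respondents report. The recorded mean is s + l.

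- *Difference in days.* With equal l in both arms, (s₁ + l) − (s₀ + l) = s₁ − s₀, which is unchanged. If l differs by d between arms, the recorded difference is off by d.
- *Ratio of days.* (s₁ + l)/(s₀ + l) moves towards 1 as l grows. Illustration with assumed values s₁ = 0.8, s₀ = 1.2 and l = 1.9: the true ratio is 0.8/1.2 = 0.67 and the recorded ratio is 2.7/3.1 = 0.87, while the difference stays at 0.4 days.
- *Yes/no.* If a share q reports other leave independently of sickness, the recorded probability is 1 − (1 − p)(1 − q). The risk difference shrinks by the factor (1 − q).
- *Variance.* With independence, the ratio of recorded to true variance is (SDₛ² + SDₗ²)/SDₛ².

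**Illustrative size (all inputs assumed; none is in the documents).** Sick days have mean 1; leave is independent of sickness and equal in both arms.

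| SD sick | Mean leave | SD leave | Share not sick leave | Variance ratio |
|---|---|---|---|---|
| 4 | 1 | 2 | 1/2 = 50% | 20/16 = 1.25 |
| 3 | 1 | 2 | 50% | 13/9 = 1.44 |
| 4 | 2 | 3 | 2/3 = 67% | 25/16 = 1.56 |
| 3 | 2 | 3 | 67% | 18/9 = 2.0 |
| 4 | 2 | 4 | 67% | 32/16 = 2.0 |
| 3 | 2 | 4 | 67% | 25/9 = 2.78 |

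The standardised effect would be multiplied by 1/√1.25 = 0.89 down to 1/√2.78 = 0.60.

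**Dependence on reporting.** Assume 25 leave days a year, or 25/13 = 1.9 per four weeks, and sickness absence of 4–6% of 20 working days, or 0.8–1.2 days. If every leave day is reported, the share of recorded days that is not sick leave is 1.9/3.1 = 61% to 1.9/2.7 = 70%. If a tenth is reported, it is 0.19/1.39 = 14% to 0.19/0.99 = 19%. If none is reported, it is zero. The fraction of leave reported drives the result, and the documents say nothing about it.

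**The case against.** A reader might infer that holidays are in fact counted as sick leave and that most recorded days will not be sickness. The documents do not support that, for four reasons.

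- The questionnaires are in Dutch and the item comes from a named instrument. Its Dutch wording, heading and instructions are not shown and may already limit it to illness. The fault would then lie only in the printed translation.
- The answer speaks of days of work missed. Many people would not describe planned leave that way, so complete over-reporting is an extreme case.
- Leave that is equal in both arms cancels from the expected difference in days, so it is wrong to say that it dilutes every effect.
- Imbalance between arms is only a possibility. Teams are matched on work setting and size, belong to one organization, and share the same measurement schedule.

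It can also be said that the outcome is secondary, is not among the secondary outcomes listed in the abstract, and does not feature in the stated hypotheses, which concern stress and the implementation of interventions.

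All of this limits how strongly the point can be put. It does not remove the mismatch. The article prints the question and its answer in full, says there is no other item, and restricts every neighbouring item to health problems. This is not detail lost by condensing a longer protocol. Matching on setting and size also does not guarantee that leave is balanced within a four-week window.

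**Conclusion.** The point holds for the printed text: the sole measure of sick leave neither restricts absence to illness nor records a reason, so other leave can be reported as sick leave. The consequences are extra variance in the days outcome and attenuation of yes/no or relative comparisons. Bias in the difference in days follows only if other leave differs between arms.

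The size cannot be derived from the documents. Under the assumed inputs above, the share of recorded days that is not sick leave runs from zero to about 70%, depending mainly on how much leave is reported; the upper end requires every leave day to be entered. The variance ratios of 1.25 to 2.78 rest on assumed SDs, independence and equal leave in both arms. Whether the problem exists in the administered questionnaire depends on the Dutch item. The primary outcome, its analysis and the sample size are untouched.

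**What to change.** First check the Dutch item, including any heading or instruction above it.

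- If it carries no health restriction, add *because of illness or health problems* to both the question and the days-missed answer, and use the same wording at baseline, six and 12 months so that the answers are comparable.
- If it already carries the restriction, leave the questionnaire alone and correct the printed English.

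The cost is a few words in one item or one line of the protocol text, with no added burden for respondents. The protocol already plans to adapt the wording of another scale, the PSC-12, so a small change of this kind fits its approach. Scaling days missed to working days is a separate analysis choice and is not needed for this fix.

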##### Implementation indicator

We aim to investigate implementation indicators to gain insight into the differences in the implementation of stress-management interventions between the intervention and control teams. First, we will collect information about the number of stress-management interventions implemented per team. Researchers will attend team meetings between the 6- and 12-month follow-up to ask the team about all interventions implemented since the start of SP@W. Second, we will include the following questions to the 12-month follow-up questionnaire: “*How often did you discuss work-related stress in your team (for example during a team meeting of your team)?”* and “*To what extent have work-related stress management interventions been implemented in your team since (month) (year)?”* The answers will be measured on a 10-point Likert Scale with 1 for “Not at all/barely” to 10 for “Very often/very much”. Both questions will be analysed at a team level to estimate an implementation score for each team.

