**Methods:**

The effectiveness of Stress Prevention@Work will be evaluated in a cluster controlled trial, in a large healthcare organization in the Netherlands, at six and 12 months. An independent researcher will match teams on working conditions and size and allocate the teams to the intervention or control group. Teams in the intervention group will be offered Stress Prevention@Work. For each intervention team, one employee is responsible for applying the strategy within his/her team using the digital platform and visiting the collaborative learning network. Using a waiting list design, the control group will be given access to the strategy after 12 months. The primary outcome is the employees’ perceived stress measured by the stress subscale of the Depression, Anxiety, and Stress Scale (DASS-21). Secondary outcome measures are job demands, job resources and the number of preventive stress measures implemented at the team level. Alongside the trial, a process evaluation, including barriers and facilitators of the implementation of Stress Prevention@Work, will be conducted in one healthcare organisation.

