##### Step 4 Implementation

In step 4, an action plan to implement the work-related stress management intervention(s) (selected in step 3) is made and the intervention is implemented. This plan includes who does what at which time in order to implement the intervention as planned. This step offers background information on how to foster good communication about the implementation of an intervention with the employees and/or management, and how to keep track of the implementation process, for example, by asking the employees how they experience the implementation of the intervention.

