### Allocation and matching teams

After the baseline measurement, teams will be matched on their specific work setting (e.g. home-based care or nursing home care) and team size. The aim is to have both comparable teams and an equal number of participants in the intervention and control condition. This information will be obtained from the team coaches. Following the match, allocation to the two conditions will be performed by an independent researcher who does not have information about the perceived stress levels in the teams. After allocation, the teams are informed about the condition they are assigned to: intervention or control (waiting list) condition. A secure login code for the digital platform (DP) for all intervention teams will be sent to the employees responsible for applying SP@W within their team. The use of the DP will be explained during a training by an implementation expert. An invitation for this training will be sent to all responsible employees for the intervention teams. They will also receive an invitation for collaborative learning network meetings and the contact information of all employees responsible for the DP in the intervention teams.

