## Discussion

This paper described the study protocol of the multifaceted and integral stress prevention strategy, SP@W. It is hypothesized that after a successful implementation of SP@W, the strategy will increase the mean number of work-related stress management interventions implemented within the intervention teams compared to the control teams and lead to a decrease in employee stress over 12 months.

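### The team count of stress-management interventions rests on self-report by teams that know their arm, and only intervention teams have a platform that labels such activities, so the comparison is at risk of bias, plausibly towards SP@W

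*Protocol article*

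**What the plan says.** The Methods part of the abstract lists the count among the secondary outcomes: "Secondary outcome measures are job demands, job resources and the number of preventive stress measures implemented at the team level". The Discussion makes it the first part of the hypothesis, namely that "the strategy will increase the mean number of work-related stress management interventions implemented within the intervention teams compared to the control teams".

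The section Implementation indicator gives the method: at some point between the 6-month and 12-month measurements, researchers go to team meetings "to ask the team about all interventions implemented since the start of SP@W". Its purpose is "to gain insight into the differences in the implementation of stress-management interventions between the intervention and control teams". The same section adds two 10-point items to the 12-month questionnaire. One asks how often work-related stress was discussed in the team. The other asks how far interventions were implemented since a stated month and year.

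On masking, Allocation and matching teams says: "After allocation, the teams are informed about the condition they are assigned to: intervention or control (waiting list) condition". The only safeguard described there concerns the assignment itself: "allocation to the two conditions will be performed by an independent researcher who does not have information about the perceived stress levels in the teams".

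On the platform, Step 3 describes a search engine that links risk factors to described interventions, and also allows teams to select interventions the organisation already has. Step 4 adds an action plan: "This plan includes who does what at which time in order to implement the intervention as planned". Login codes go to the intervention teams only. Under Study design and measurements, control teams are offered SP@W after the 12-month measurement.

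**The concern.** The count depends on what a team recognises as a stress-management intervention and remembers to mention. SP@W itself may change that recognition. An intervention team has worked with a catalogue that names interventions, has planned them and is asked to evaluate them. A control team has to decide without that help which of its activities qualify.

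The overlap in content makes this concrete. Because Step 3 lets teams select measures already present in the organisation, one existing measure can carry the label in an intervention team and go unlabelled in a control team.

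What is at stake is the implementation claim. The Background presents SP@W as an answer to an implementation problem and expects it to lower stress through more implementation. If the count is higher in the intervention arm, the stated method cannot separate more activity from readier labelling of the same activity.

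**Working it through.** The document gives no figure for how completely teams report. Its only calculated figure, the sample size, concerns the DASS-21 stress subscale and has no bearing here. The check is therefore a comparison of the arms on what the document states, followed by an illustration under assumptions.

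**1. The arms side by side when the count is taken (between 6 and 12 months)**

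| Feature | Intervention teams | Control teams | Source |
|---|---|---|---|
| Know their condition | Yes | Yes | Allocation and matching teams |
| Platform access | Yes | No, offered after 12 months | Allocation and matching teams; Study design and measurements |
| Catalogue linking risks to named interventions | Yes | No | Step 3 |
| Existing measures can be selected as interventions | Yes | No such step | Step 3 |
| Action plan | Yes | None through SP@W | Step 4 |
| Source of the count | Team's answer at a meeting | Team's answer at a meeting | Implementation indicator |

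The source of the count is the same in both arms. What differs is the labelling and planning that precede the answer. The platform's records are not named as a source for the count, so they can act only through what the team recognises and recalls.

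**2. How differential reporting would act**

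Let m be the true mean number of activities per team, equal in both arms, and let r_I and r_C be the proportions reported in intervention and control teams. The observed means are m × r_I and m × r_C. The observed ratio is r_I / r_C and does not depend on m; the spurious difference is m × (r_I − r_C).

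**3. Illustration (m, r_I and r_C are all assumptions)**

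With m = 3 and r_I = 0.9:

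| r_C | Observed means | Difference | Ratio |
|---|---|---|---|
| 0.9 | 2.7 and 2.7 | 0.0 | 1.0 |
| 0.8 | 2.7 and 2.4 | 0.3 | 1.1 |
| 0.7 | 2.7 and 2.1 | 0.6 | 1.3 |
| 0.6 | 2.7 and 1.8 | 0.9 | 1.5 |
| 0.5 | 2.7 and 1.5 | 1.2 | 1.8 |

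Over r_I from 0.8 to 1.0 and r_C from 0.5 to 0.9, with r_C not above r_I, the ratio runs from 1.0 (equal reporting) to 1.0/0.5 = 2.0. If control teams reported more fully, the bias would reverse: r_I = 0.8 and r_C = 0.9 give 0.8/0.9 = 0.89.

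**4. Whether other data in the plan would settle it**

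- The two 12-month items go to both arms and give context, but they are also self-report by employees who know their arm.
- Platform logs and meeting notes are named under Process evaluation, not for the count.
- The stakeholder interviews under Co-interventions are not linked to the count.
- Strengths and limitations discusses matching and contamination, not ascertainment of this outcome.

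**The case against.** The strongest reply is that much of the case could rest on the article's silence. It gives no question wording for the team meetings and does not say whether a list or definition is used. Such details are often left to a full protocol. The same question may be put to both arms, and team self-report is hard to avoid in a waiting-list trial of an organisational strategy. The count also does not stand alone. The item on how often stress was discussed would capture, in both arms, some of the informal talks that a control team might not call an intervention. And a guideline-based dialogue is not the same thing as an informal talk, so counting one and not the other may reflect a real difference.

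Most of this limits the point without removing it. Several stronger readings are tempting, and the document does not support them:

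- **That the question is open.** This would be inferred only from the absence of a stated list.
- **That the researchers who ask know the arm.** Knowledge of the arm is documented for the teams only; for the researchers the article says nothing either way.
- **That the question is framed around SP@W.** The reference to the start of SP@W describes the look-back period to readers and is not quoted question wording. Where the section does quote wording for the same construct, it is neutral and calendar-dated.
- **That the count favours SP@W through ascertainment alone.** The direction is plausible, not established. Control teams might list loosely related activities, and intervention teams might report only what they chose through the platform.

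What remains is what the article does state: the count comes from teams that know their condition, and only one arm has a tool that labels and plans the things being counted.

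**Conclusion.** The concern holds as a risk of differential ascertainment in a named secondary outcome that carries its own hypothesis. The plausible direction is towards SP@W. The size is unknown: the ratios of 1.0 to 2.0 show what assumed reporting rates would do and are not an estimate for this trial. Equal reporting would leave no bias.

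The primary outcome is unaffected, because DASS-21 stress does not use the count. The change is worth making because it is cheap and because, under the stated method, a higher count would be hard to interpret as more implementation.

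**What to change.** Under Implementation indicator:

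1. Set one definition of a countable stress-management intervention that refers neither to SP@W nor to the platform.
2. Ask the same neutrally worded question of every team in both arms, with the month-and-year anchor that the 12-month questionnaire item already uses as the start of the look-back period.
3. Record each activity as the team describes it. Have an existing researcher code and count the de-identified records against the definition, with team and arm removed.
4. If prompts are used, keep them generic. Prompts drawn from the platform's catalogue would show control teams part of the intervention's content before the 12-month primary outcome, and the article already names contamination as a limitation.
5. Interpret the count alongside the two 12-month items, and state that these too are unmasked self-report.

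The cost is a short written definition and a little extra coding of answers that the team visits already collect. Masking at the coding stage may be incomplete where a described activity reveals the arm. A neutral question does not remove the teams' own knowledge of their condition, so the fix reduces the risk and does not abolish it.
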